| 4. An exclusion criteria that was existed before recruitment but was discovered afterwards.                                                                                                                                                                                                                                                                                                                                                                                                                                                                                                                                                                                                                                                                                       | 233
234                                                  |
| Study design: Multicenter open label randomized controlled trial.                                                                                                                                                                                                                                                                                                                                                                                                                                                                                                                                                                                                                                                                                                          | 235                                                         |
| Number of estimated medical centers: 3                                                                                                                                                                                                                                                                                                                                                                                                                                                                                                                                                                                                                                                                                                                                            | 236                                                         |

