| 2. Cervical dilatation of 1–4 cm accompanied by cervical effacement of at least 50%.                                                                                                                                                                                                                                                                                                                                                                                                                                                                                                                                                                                                                                                                                              | 249                                                         |
| The tocolytic treatment (first, second and third lines) will be determined by the attending physician at the time of admission and later on according to the departmental protocol. In addition, all patients will be screened for GBS (group B Streptococcus ) colonization if GBS status is unknown and urinary tract infections and treated appropriately. All patients will receive betamethasone for fetal lung maturity and appropriate GBS prophylaxis if those are indicated according to the departmental protocol. The tocolytic treatment which was successful in arresting the preterm labor will be continued for 48 hours. Arrest of preterm labor will be defined as 6 or fewer contractions per hour, intact membranes, and $\leq 4$ cm cervical dilation. | 250
251
252
253
254
255
256
257
258 |
| If the patient has an arrest of preterm labor, she will be asked to participate in this study. She will receive the first dose of the study medication at least 24 hours after initial treatment with tocolytic treatment and up to 3 days after finishing the tocolytic treatment, and then daily until 36+6 weeks or delivery (if occurs before 36.6 weeks).                                                                                                                                                                                                                                                                                                                                                                                                                    | 259
260
261
262                                    |

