| Whether the patient should receive repeated courses of tocolytics and/or betamethasone will be left to the discretion of the attending physician according to the departmental protocol.                                                                                                                                                                                                                                                                                                                                                                                                                                                                                                                                                                                                                                                | 277
278
279                                                  |
| Data collection                                                                                                                                                                                                                                                                                                                                                                                                                                                                                                                                                                                                                                                                                                                                                                                                                  | 280                                                                |

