| Study randomization                                                                                                                                                                                                                                                                                                                                                                                                                                                                                                                                                                                                                                                                                                                                                                                                              | 286                                                                |
| Randomization will be done by computerized software according to power calculation and the codes will be kept inside sealed envelopes. The randomization table will be stratified to 24.0-28.6 and 29.0-34.0 according to the day of tocolytic initiation.                                                                                                                                                                                                                                                                                                                                                                                                                                                                                                                                                                              | 287
288
289                                                  |

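### Randomisation is stratified by gestational age only, so the mix of the three hospitals between arms is left to chance: no bias, but some precision and credibility forgone

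*Protocol*

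**What the plan says.** - **Allocation** (Protocol, Study randomization): "Randomization will be done by computerized software according to power calculation and the codes will be kept inside sealed envelopes". Then: "The randomization table will be stratified to 24.0-28.6 and 29.0-34.0 according to the day of tocolytic initiation". Center is not named as a factor. The section does not say whether there is one list or one per hospital, how envelopes are divided, or whether blocks are used.
- **Setting** (Protocol, Study design): "Multicenter open label randomized controlled trial", and "Number of estimated medical centers: 3".
- **Background care before enrollment** (Protocol, Treatments, study groups, and patient management): "The tocolytic treatment (first, second and third lines) will be determined by the attending physician at the time of admission", and after that under the departmental protocol. Betamethasone and GBS prophylaxis are also given as departmental protocol indicates. One element is common to all sites: "The tocolytic treatment which was successful in arresting the preterm labor will be continued for 48 hours".
- **Background care after enrollment** (same section): repeat tocolysis and repeat betamethasone "will be left to the discretion of the attending physician according to the departmental protocol".
- **Sample size** (Protocol, Sample Size and statistics): a 7-day difference with SD 14 days (reading the ± as an SD), 64 per group, 5% two-sided alpha, 80% power; 140 women in total.

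**The concern.** Hospital is the level at which background care is allowed to vary, and it is the factor left out of the allocation scheme. If one hospital's women happen to fall more into one arm, that arm also carries more of that hospital's tocolytic and steroid practice and case mix. With 140 women over three sites such gaps are likely to be visible in the baseline table. A reader of an open-label trial may then ask how much of the difference is hospital. If hospitals do differ in days to delivery, ignoring them also leaves explainable variation in the error term.

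This belongs in the protocol because a later SAP can add center as a covariate but cannot create balance once envelopes have been opened.

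**Working it through.** **The plan's own figure.** Difference 7, SD 14, two-sided 5%: the normal approximation gives 63 per group (power 80.7% at 64). The t test gives 80.1% power at 64 and 79.5% at 63. The stated 64 per group is reproduced, and nothing below changes it.

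**Chance imbalance in center mix.** Inputs: 70 per arm (Protocol); a center's share *f* of recruits (assumed, as the protocol gives none). The SD of the between-arm difference in that share is sqrt(2·f·(1−f)/70):

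| f | SD | 1.96 × SD |
|---|---|---|
| 0.33 | 0.079 | 0.156 |
| 0.50 | 0.085 | 0.166 |
| 0.60 | 0.083 | 0.162 |

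Simulation (20,000 allocations of 140 women, 70/70, without center stratification) gives the chance that at least one center's share differs between arms by the stated amount:

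| Center sizes (assumed) | ≥10 points | ≥15 points | ≥20 points |
|---|---|---|---|
| 47/47/46 | 50% | 15% | 4% |
| 70/40/30 | 39% | 10% | 4% |
| 84/28/28 | 35% | 8% | 3% |

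The mean imbalance is zero in every case.

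**What a gap does to the estimate.** Suppose one center differs from the others by an assumed 3 to 7 days. A typical 8-point gap shifts the arm difference by 0.08 × 3 = 0.24 to 0.08 × 7 = 0.56 day. A gap at the edge of the 95% range (16 points) shifts it by 0.48 to 1.12 days. The planned standard error is 14 × sqrt(2/64) = 2.47 days, so even 1.12 days is 1.12/2.47 = 0.45 of a standard error.

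**Type I error and power.** Simulation: 128 women, three near-equal centers, total SD held at about 14, allocation not stratified by center. Center means are assumed at 0/0/0, −5/0/+5 or −7/0/+7 days around the average, so in the last two the outer centers lie 10 and 14 days apart.

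| Center means (days) | Type I error, unadjusted | Power, unadjusted | Power, center-adjusted |
|---|---|---|---|
| 0/0/0 | 4.7% | 81% | 80% |
| −5/0/+5 | 4.8% | 80% | 83% |
| −7/0/+7 | 4.9% | 79% | 86% |

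The mean estimate is about 0 under no effect and about 7 days under the planned effect, so there is no bias.

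The power gain can be checked by formula. The between-center variance for ±5 is (25 + 0 + 25)/3 = 16.7. The within-center SD is sqrt(196 − 16.7) = 13.4, the standard error is 13.4 × sqrt(2/64) = 2.37, and power is Φ(7/2.37 − 1.96), about 84%. For ±7 the variance is 32.7, the SD 12.8, the standard error 2.26 and the power about 87%. These are slightly above the simulated values because the formula ignores the t distribution and the cost of estimating center terms. For a smaller spread of ±3.5 days (outer centers 7 apart), the variance is 8.2, the SD 13.7, the standard error 2.42 and the power about 82%, against 81% by the same formula with no center effect.

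The adjusted column was obtained with allocation not stratified by center. The power gain therefore comes mainly from using center in the analysis. What per-center lists add is balance, and an estimate that depends little on whether center is adjusted for.

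**The case against.** **Strongest case against.** Stratifying by gestational age already covers a factor that bears directly on both primary outcomes, and adding center is a design option. The imbalance is random and already allowed for in the test's error rate, and the planned 80% power is kept. Center effects of several days are unsupported. The protocol's Introduction says tocolytics help for only about two days, women enter only after labor has been arrested, and the successful agent is continued for the same 48 hours everywhere. Center adjustment may also stand in an SAP that is not shown. All of this stands, and it limits the point to efficiency and credibility. It does not remove the case for a better list, because balance can only be built in at allocation.

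**Stronger readings that a reader might infer, and that the documents do not support:**

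- *That the result will be confounded by background care.* The initial tocolytic is chosen before randomisation, so it is balanced in expectation. The simulation shows no bias and no inflated type I error.
- *That a single shared list must be split across three hospitals.* The section speaks of one randomization table, which hints at this, but it does not say so. Per-center envelope sets are not ruled out.
- *That the stratification scheme causes arm differences in rescue tocolysis or repeat steroids.* These come after randomisation, at the discretion of unblinded physicians, and repeat tocolysis is itself a secondary outcome. Center lists can balance departmental policy but cannot stop arms being treated differently within a hospital. That is a separate issue.

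**Conclusion.** The point holds as an inexpensive improvement to the allocation scheme and not as an error in the plan. Center mix is left to chance: the SD is about 8 points per center, and the chance of a gap of 10 points or more somewhere is about 35% to 50%, depending on center sizes. Validity is intact.

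The loss is at most modest. It is nil if centers do not differ, and about 3 to 6 power points against an unadjusted 80% or so if center means are spread by ±5 to ±7 days. Center sizes and center effects are assumptions throughout. That center balance is not secured is inferred from the only factor named, since the text is silent on per-center lists.

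**What to change.** - Generate a separate blocked list, stratified by the two gestational-age bands, for each hospital, and issue a separate envelope set to each. This gives 3 × 2 = 6 strata, about 140/6 = 23 women each on average.
- Vary the block sizes and do not disclose them to recruiting staff, because the trial is open label. If recruitment has begun, the new lists can apply only to women not yet randomised.
- State in Study randomization that lists and envelopes are per center. If they already are, that sentence is all that section needs on this point.
- Account for center and gestational-age stratum in the primary comparisons, if the SAP does not already do so. The two changes go together: with per-center lists and an analysis that ignores center, the standard error would be somewhat too large whenever centers differ.

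**Cost.** A new computer-generated list, three envelope sets and center terms in the model. Some blocks will stay unfinished, more so if a hospital recruits few women. Allocation within a center becomes slightly more predictable, which varying block sizes reduce but do not remove. Eligibility, treatment, visits and sample size are unchanged.

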**Abstract**

8

**Background:** Preterm labor is the leading cause of neonatal mortality and morbidity. Therefore, once preterm labor is diagnosed before 34 weeks of gestation, tocolytic therapy is initiated in an effort to prolong the pregnancy. Despite meticulous research for useful tocolytics, the medications that are available for this indication have been proven useful for only approximately two days, and searching for a more useful agent for labor arrest is imperative. It has been suggested that progesterone derivatives are useful in preventing preterm labor in women with cervical shortening or preterm labor in the past. However, the impact of progesterone has not been sufficiently tested for pregnancy prolongation after tocolytic therapy.

**Working hypothesis and aims:** Since progesterone derivatives are useful in preventing preterm labor in cases of risk factors or previous preterm labor, they will also show efficacy in pregnancy prolongation in women whose preterm labor was arrested following tocolytic treatment. The study aim is to evaluate the efficacy of vaginal progesterone for the prolongation of pregnancy after arrested pre-term labor.

**Methods:** Multicenter randomized controlled trial. Patients diagnosed with arrested pre-term labor following tocolytics at 24-34 gestational weeks will be randomly allocated to receive either vaginal micronized progesterone 400 mg/day (200 mg\*2/day) or no treatment. The primary outcomes are the mean number of days from enrollment to delivery and the rate of preterm delivery prior to 37 weeks of gestation. Secondary outcomes include need for additional tocolytic therapy, the rate of pregnancies prolonged for at least one week, neonatal complications, and admission to neonatal intensive care unit.

Assuming mean difference between the groups of 7 days  $\pm$  14 days a sample size of 64 women per group will be required (5% two-sided alpha, 80% power). This sample size is sufficient to detect a reduction from 50% to 25% in the rate of women who delivered prior to 37 weeks (5% two-sided alpha, 84% power). Considering 10% drop outs, 140 women will be required for this study (70 per group).

**Expected results:** Progesterone will be useful to prolong pregnancy after preterm labor was arrested with tocolytics.

**Importance:** This study has the potential to find a treatment to prevent preterm labor and thus to dramatically reduce neonatal morbidity and mortality.

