| • Nausea                                                                               | 304 |
| • Dizziness                                                                            | 305 |
| Severe adverse effects (e.g., anaphylaxis) will be reported to the Helsinki Committee. | 306 |
| Sample Size and statistics                                                      | 307 |
| Assuming mean difference between the groups of 7 days $\pm$ 14 days a sample size of   | 308 |
| 64 women per group will be required (5% two-sided alpha, 80% power). This sample       | 309 |
| size is sufficient to detect a reduction from 50% to 25% in the rate of women who      | 310 |
| delivered prior to 37 weeks (5% two-sided alpha, 84% power). Considering 10% drop      | 311 |
| outs, 140 women will be required for this study (70 per group).                        | 312 |
|                                                                                        | 313 |
| Patients' confidentiality                                                | 314 |
| Patients' personal information will be kept in sealed brown envelop separated from     | 315 |
| the CRF. Each patient will receive a code number written beside the patient name       | 316 |
| inside the aforementioned envelop. Only the patient's code will be written in the CRF  | 317 |
| form. All study data will be regarded in a locked closet inside a closed room.         | 318 |
|                                                                                        | 319 |

|                                                                                                                                                                                                                                                                                                                                 |                          |
|---------------------------------------------------------------------------------------------------------------------------------------------------------------------------------------------------------------------------------------------------------------------------------------------------------------------------------|--------------------------|

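### Seventy women per group less 10% drop-outs leaves 63, one short of the 64 per group that the protocol says it requires; the effect on power is minor

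*Protocol*

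**What the plan says.** Sample Size and statistics, read in order, gives every input and the result:

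- The effect for the first primary outcome, days from enrollment to delivery: "Assuming mean difference between the groups of 7 days $\pm$ 14 days a sample size of"
- The requirement that follows from it: "64 women per group will be required (5% two-sided alpha, 80% power). This sample"
- The second primary outcome at the same size: "size is sufficient to detect a reduction from 50% to 25% in the rate of women who"
- Its power, and the start of the drop-out sentence: "delivered prior to 37 weeks (5% two-sided alpha, 84% power). Considering 10% drop"
- The enrolment figure: "outs, 140 women will be required for this study (70 per group")

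The Methods part of the Abstract gives the same calculation and closes the same way: "Considering 10% drop outs, 140 women will be required for this study (70 per group"). Neither place gives a formula or a rounding rule for the drop-out allowance.

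The protocol also lists criteria for removing a patient from the study: refusal after enrollment, no data because of loss to follow-up, a new allergy to the study drug, and an exclusion criterion found after recruitment. These are losses from among the women enrolled.

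**The concern.** A drop-out allowance exists so that the required number remains after the expected losses. Here the required number is 64 per group, the expected loss is 10%, and the enrolled number is 70 per group. Taking 10% from 70 gives 63, so the enrolled number does not meet the condition it was set to meet. The protocol states all three figures itself, twice, so this can be judged without any further document.

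At stake is the accuracy of the sample-size statement: whether 140 women, with the losses the protocol plans for, give the power it quotes for its two primary outcomes.

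**Working it through.** **Inputs, all from Sample Size and statistics.** Mean difference 7 days; the ± 14 days read as the common standard deviation, so the standardised effect is 7/14 = 0.5; two-sided alpha 5%; power 80%; 64 per group required; rates 50% and 25% with 84% power; drop-out 10%; 70 per group, 140 in total.

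**Reproducing the plan's own figures.**

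- Days to delivery, two-sample t-test (noncentral t): the solution is n = 63.77, rounded up to 64 per group. Power at 64 is 80.1%. The stated 64 and 80% are reproduced.
- The same by the normal approximation: n = 2 × (1.960 + 0.842)² × (14/7)² = 62.79, rounded up to 63. The stated 64 is therefore the t-test figure.
- Preterm delivery, two proportions without continuity correction: power = Φ{[0.25√n − 1.960√(2 × 0.375 × 0.625)] / √(0.25 + 0.1875)}. At n = 64 this is Φ{(2.000 − 1.342)/0.661} = 84.0%. The stated 84% is reproduced.

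**The drop-out step.**

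- Women left from 70 after 10% loss: 70 × (1 − 0.10) = 63 per group, 126 in total, against 64 and 128.
- Number to enrol so that 64 remain: 64/(1 − 0.10) = 71.1, so 72 per group and 144 in total. Inflating the total instead gives 128/0.9 = 142.2, so 143.
- Largest loss at which 70 still leaves 64: 1 − 64/70 = 8.6%. At 8.5%, 70 × 0.915 = 64.05.

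**Power at the number that remains.**

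| | 64 per group | 63 per group |
|---|---|---|
| Days to delivery, t-test | 80.1% | 79.5% |
| Days to delivery, normal approximation | 80.7% | 80.1% |
| 50% vs 25% | 84.0% | 83.4% |

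The loss is about 0.6 percentage points on each primary outcome.

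**The case against.** The strongest case against raising this is that it decides nothing. The 7 days, the 14 days, the 50% and 25% and the 10% are round planning assumptions, and a gap of 1.4 points between 10% and 8.6% drop-out is far smaller than the uncertainty in any of them. The protocol gives power in whole percents, and 79.5% (79.52% before rounding) still rounds to 80%. All of this stands, and it limits the point to a correction of wording. It does not make the statement right: 64 required, 10% lost and 70 enrolled cannot all hold together.

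Two stronger readings are tempting, and the documents support neither.

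- *A reader might infer that the trial fails to deliver 80% power.* By the t-test, power falls under 80% by half a point at most; by the normal approximation it is 80.1% at 63 per group. The stated 84% refers to 64 per group and is correct there; at 63 it becomes 83%.
- *A reader might infer that 64 was multiplied by 1.1 and the result rounded down.* That fits, since 64 × 1.1 = 70.4. But 63/0.9 = 70.0 fits exactly as well, 63 being the normal-approximation sample size for the same inputs. The protocol shows neither route. The mismatch does not depend on which was used: on the second route, 70 would rest on 63 while the text says 64.

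**Conclusion.** The point holds as a minor inconsistency. At the protocol's own drop-out rate, 70 per group leaves 63 women and not the 64 stated as required. The shortfall is one woman per group after losses (126 against 128 in total). Expressed as enrolment it is four women, 144 against 140 or 2.9%, when each group is rounded up, and three when only the total is inflated. The cost is about 0.6 points of power on each primary outcome.

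This rests on three assumptions: that ± 14 days is the common standard deviation, which is what reproduces the 64; that the 10% is a fraction of the women enrolled, which agrees with the removal criteria; and that losses are equal in the two groups. How the 70 was reached remains unknown. The finding gives no ground for calling the trial underpowered or for asking that more women be enrolled.

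**What to change.** Keep 140 women and reword the drop-out sentence in both the Abstract and Sample Size and statistics, in one of two ways:

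- say that 70 per group allows for about 8.5% drop-out while leaving 64 per group; or
- keep 10% and say that it leaves 63 per group, with about 79.5% power for days to delivery (t-test) and about 83% for 50% against 25%.

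Should the sponsor wish to keep both the 10% and the 64, the matching enrolment is 72 per group (144), since 72 × 0.9 = 64.8. That is given for reference and is not needed to settle the point.

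The cost is one sentence in two places and a slightly less favourable stated drop-out allowance or power. Either rewording leaves recruitment, analysis and patient care unchanged.
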